#### Secondary outcomes

2.4.2

Secondary endpoints include diagnostic sensitivity and specificity, defined as the proportion of true severe influenza cases correctly identified by the model or clinicians, which reflects the tool’s capacity to minimize missed diagnoses in high-risk populations (30).

#### Subgroup analyses

2.4.3

Predefined subgroup analyses will assess heterogeneity in model performance across key variables to evaluate the impact of local healthcare infrastructure and influenza epidemiology.

patient characteristics: age (infants, children, adults, older adults), comorbidities (cardiovascular disease, diabetes), and vaccination status (yes, no);clinician factors: experience level (resident, attending, chief physician);hospital resource tier: urban or rural facilities;geographic variation: northern or southern regions of Jiangsu Province.

These analyses aim to identify subgroups where the model excels or underperforms, informing targeted clinical deployment. Statistical adjustments, such as Bonferroni correction for multiple comparisons and multivariable regression for confounders, will ensure robust interpretation of subgroup differences.

#### Handling missing data

2.4.4

To address missing data, variables with more than 20% missing values will be excluded to ensure reliability. For remaining gaps, the Multivariate Imputation by Chained Equations (MICE) package in R will be employed, leveraging iterative modeling across variables to impute missing values under the missing-at-random assumption. This method preserves dataset integrity by estimating missing entries based on observed patterns, thereby minimizing bias while maintaining statistical power.

#### Adjudication of ground truth

2.4.5

To ensure accurate outcome classification, an independent adjudication panel comprising three senior infectious disease specialists will retrospectively review all cases classified as severe influenza, verifying endpoints such as ICU admission, mechanical ventilation, or mortality. Discrepancies in outcome assessments among panel members will be resolved through majority vote, with detailed documentation of dissenting opinions. This rigorous process minimizes misclassification bias and enhances the reliability of outcome data, serving as the gold standard for model and clinician performance evaluation.

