#### Phase overview

2.1.4

The study comprises five sequential phases, which is based on the multiple nesting approach used in [name]’s past methods (16–20).

Model development: retrospective data (2019–2024) from 87 hospitals for training and internal validation.External validation-comparative study: benchmarking model performance against clinician diagnoses.Multi-reader, multi-case validation: assessing inter-physician variability with/without model assistance.Randomized controlled trial: evaluating real-time diagnostic accuracy in a clinician-AI collaborative setting.Prospective validation: real-world testing during the 2025 influenza season.

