#### Phase I: model development and internal validation

2.3.1

This phase utilizes retrospective EHRs from 87 hospitals (Table 1) in Jiangsu Province (from January 2019 to December 2024), encompassing four key data categories:

Demographics: age, sex, vaccination history, and comorbidities.Clinical symptoms: fever duration, cough frequency, dyspnea severity, and other symptoms detailed (Table 2).Laboratory/imaging data: viral subtype (confirmed via RT-PCR), blood cell counts, and chest X-ray/computed tomography (CT) findings.Outcomes: severe influenza progression and mortality, defined as intensive care unit (ICU) admission or mechanical ventilation.

**Table 1 tab1:** Datasets distribution.

City	Hospitals
Nanjing	Jiangsu Provincial People’s Hospital, General Hospital of the Eastern Theater Command, Nanjing Drum Tower Hospital, Jiangsu Provincial Hospital of Traditional Chinese Medicine, Zhongda Hospital Affiliated to Southeast University, Nanjing First Hospital, The Second Affiliated Hospital of Nanjing Medical University, Nanjing Hospital of Traditional Chinese Medicine
Wuxi	Wuxi People’s Hospital, The Affiliated Hospital of Jiangnan University, Wuxi Hospital of Traditional Chinese Medicine
Xuzhou	The Affiliated Hospital of Xuzhou Medical University, Xuzhou Central Hospital, Xuzhou First People’s Hospital, Xuzhou Mining Group General Hospital, Xuzhou Hospital of Traditional Chinese Medicine
Changzhou	Changzhou First People’s Hospital, Changzhou Hospital of Traditional Chinese Medicine, The Third Affiliated Hospital of Soochow University (Changzhou Second People’s Hospital)
Suzhou	The First Affiliated Hospital of Soochow University, The Second Affiliated Hospital of Soochow University, Suzhou Municipal Hospital, Suzhou Hospital of Traditional Chinese Medicine
Nantong	The Affiliated Hospital of Nantong University, Nantong First People’s Hospital, Nantong Hospital of Traditional Chinese Medicine
Lianyungang	Lianyungang First People’s Hospital, Lianyungang Hospital of Traditional Chinese Medicine, Lianyungang Second People’s Hospital
Huai’an	Huai’an First People’s Hospital, Huai’an Second People’s Hospital, Huai’an Hospital of Traditional Chinese Medicine
Yancheng	Yancheng First People’s Hospital, Yancheng Hospital of Traditional Chinese Medicine, Yancheng Third People’s Hospital
Yangzhou	Subei People’s Hospital, Yangzhou First People’s Hospital, Yangzhou Hospital of Traditional Chinese Medicine

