#### Phase IV: randomized controlled trial

2.3.4

This phase is a pragmatic randomised controlled design to assess the effectiveness of AI-assisted diagnosis in the real world. Clinicians will be assigned in a 1:1 ratio to either the control group (using standard clinical assessment protocols) or the AI model-assisted group. Allocation will be by block group randomisation, stratified by hospital level (urban vs. rural) and clinician experience level (resident, attending, chief) to ensure balanced representation in key subgroups.

The control group will rely exclusively on routine diagnostic workflows, while the model-assisted group will integrate AI outputs into their decision-making process and retain full authority to accept or reject recommendations. The primary outcome is the between-group AUC difference, with a ΔAUC greater than 0.15 defined as clinically significant, which is consistent with the U.S. Food and Drug Administration’s (FDA) benchmarks for diagnostic tools based on artificial intelligence or machine learning (AI/ML). The design simulates real-world clinical practice and quantifies the added value of AI in improving diagnostic accuracy while preserving clinician autonomy.

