#### Blinding (masking)

2.6.2

To minimize bias, a single-blind design will be implemented for clinicians: those in the control group will remain unaware of their allocation status and the existence of the AI model, while clinicians in the model-assisted group will access predictions through a neutral interface labeled as a “Decision Support Tool,” avoiding explicit references to AI. Patients will be fully blinded to group assignments, with informed consent documents describing participation in “a study to improve influenza diagnosis” without disclosing AI involvement. Independent outcome adjudicators assessing severe influenza outcomes will also remain blinded to group allocations and model outputs, ensuring objective evaluation of clinical endpoints. This multi-layered blinding strategy safeguards against performance and detection bias, maintaining the trial’s scientific rigor.

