#### Intervention groups

2.6.3

In the control group, clinicians (without any AI assistance) will diagnose influenza cases using standard clinical protocols, integrating symptoms, laboratory results, and imaging findings. Patients in this group will receive routine care based solely on clinician assessments.

In contrast, the model-assisted group will utilize a secure digital dashboard providing real-time AI predictions, including a risk score (0–100%) for severe influenza progression and highlighted contributing factors (such as prolonged fever duration, abnormal lymphocyte counts).

While the model offers data-driven insights, its outputs are non-prescriptive; clinicians retain full authority to accept, modify, or reject recommendations, ensuring clinical judgment remains central to decision-making. This design balances technological support with practitioner autonomy, reflecting real-world diagnostic workflows.

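### ICU admission alone can make a case severe, so if Phase IV assesses live patients the AI-informed call can influence its own reference standard and may bias the between-arm AUC difference in either direction

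*Protocol article*

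**What the plan says.** **The label.** Section 2.3.1 gives the outcome as "severe influenza progression and mortality, defined as intensive care unit (ICU) admission or mechanical ventilation". In section 2.4.5 a panel of three specialists "will retrospectively review all cases classified as severe influenza", "verifying endpoints such as ICU admission, mechanical ventilation, or mortality", with the result "serving as the gold standard for model and clinician performance evaluation". No criterion independent of a care decision is required, so ICU admission by itself is enough.

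**Phase IV.** Section 2.1.4 describes this phase as "evaluating real-time diagnostic accuracy in a clinician-AI collaborative setting", and section 2.7.2 places Phases III to V in prospective data collection. Under section 2.3.4, "the model-assisted group will integrate AI outputs into their decision-making process", and the primary outcome is the between-group AUC difference, with more than 0.15 counted as clinically significant. For the control group, section 2.6.3 says: "Patients in this group will receive routine care based solely on clinician assessments".

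**Blinding.** Section 2.6.2 states: "Independent outcome adjudicators assessing severe influenza outcomes will also remain blinded to group allocations and model outputs".

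**Phase V.** Under section 2.3.5, predictions reach clinicians within 2 hours of case entry. Diagnoses are recorded before and after the model is seen, and model predictions are compared with adjudicated severe influenza.

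**The concern.** A reference standard should not depend on the test result being judged. ICU admission is a decision, and the clinician whose call is scored may contribute to it. Two distortions follow, and they act in opposite directions:

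- A high score prompts a call of severe and a precautionary ICU admission. The call then counts as correct because of what it triggered.
- A high score prompts early attention and the patient never reaches an endpoint. A correct call then counts as a false positive. The panel reviews only cases already classified as severe, so it would not look at this one again.

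Blinded adjudicators can read a chart without bias, but they still confirm an admission that took place. Control clinicians' calls may also influence ICU use, which could offset part of the effect. Even so, only one arm's calls are informed by the score, so the two arms' labels would not arise in the same way. The primary contrast would then mix diagnostic accuracy with a change in ICU use.

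**Working it through.** The plan gives no figure for this effect. The relevant figures in it are the threshold (ΔAUC above 0.15, sections 2.3.4, 2.4.1 and 2.8.1) and the planned effect (0.85 − 0.70 = 0.15, section 2.5.1). The planned effect lies exactly at the threshold, so a small shift in the estimate can change the conclusion. Everything else below is assumed.

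**Check 1: a single yes/no call, no true difference between arms.** Assume 20% truly severe and sensitivity = specificity = 0.70 in both arms. For a binary call, AUC = (Se + Sp)/2 = 0.70. Per unit of population: TP = 0.20 × 0.70 = 0.14, FN = 0.06, FP = 0.80 × 0.30 = 0.24, TN = 0.56.

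Precautionary admission: in the assisted arm a share q of false positives goes to the ICU and is relabelled severe. Then Se = (0.14 + 0.24q)/(0.20 + 0.24q) and Sp = 0.56/(0.80 − 0.24q).

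- q = 0.1: Se = 0.164/0.224 = 0.732, Sp = 0.56/0.776 = 0.722, AUC = 0.727
- q = 0.2: Se = 0.188/0.248 = 0.758, Sp = 0.56/0.752 = 0.745, AUC = 0.751
- q = 0.3: Se = 0.212/0.272 = 0.779, Sp = 0.56/0.728 = 0.769, AUC = 0.774

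Averted progression: 20% of true positives lose the endpoint. Se = 0.112/0.172 = 0.651, Sp = 0.56/0.828 = 0.676, AUC = 0.664.

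The spurious difference is therefore +0.03 to +0.07 in one direction and about −0.04 in the other.

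**Check 2: graded ratings.** Binormal simulation, 1,000,000 patients per scenario. Control AUC is 0.70 and assisted AUC is 0.70 or 0.85. Severe prevalence is 10% or 20%, and the label responds in the assisted arm only, among the top-rated share of patients equal to the prevalence. In that group, 5% to 30% of patients who would not be severe are admitted to the ICU, or 5% to 30% of those who would be severe are averted.

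| Prevalence | Simulated ΔAUC, label unaffected | With precautionary ICU (5% to 30%) | With averted progression (5% to 30%) |
|---|---|---|---|
| 10% | −0.002 | 0.009 to 0.059 | −0.006 to −0.029 |
| 20% | 0.000 | 0.010 to 0.057 | −0.007 to −0.047 |
| 10% | 0.152 | 0.157 to 0.178 | 0.147 to 0.121 |
| 20% | 0.149 | 0.153 to 0.174 | 0.141 to 0.100 |

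The small departures from 0 and 0.15 in the second column are simulation error. With no true effect, neither check comes near 0.15. With a true difference near 0.15, a 5% reaction is already enough to move the estimate across the threshold: 0.149 to 0.153, or 0.152 to 0.147.

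**Is the Phase IV setting live?** For: real-time evaluation (2.1.4), prospective collection (2.7.2), control patients' care resting on clinician assessment (2.6.3), patients blinded to group (2.6.2), and provisions for override and emergency unblinding (3.1). Against: section 2.3.4 also says the design simulates practice, sections 2.4.1 and 2.8.1 plan a multi-reader, multi-case analysis, and section 2.5.3 counts retrospective patients among the 348. The first group fits the text better, but the second leaves room for shared or historical cases.

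**The case against.** The strongest reply is that the arm-specific mechanism is inferred. The sentence tying care to clinician assessment covers the control group only, and no section says that the rating clinician decides on ICU admission. The Dorfman-Berbaum-Metz method in its usual form has readers score common cases. If both arms read the same or historical cases, the label is common to both and this bias disappears. That stands, and it makes the point conditional on live patients.

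Hard clinical events confirmed by a blinded independent panel are also a defensible endpoint. That stands too, and it is a reason to keep the endpoint and add a check on it.

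Three stronger readings are tempting but not supported:

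- *A positive trial could arise with no diagnostic gain.* The illustrations reach at most about 0.07 from zero, well short of 0.15.
- *The difference is inflated.* The direction is unknown, since averted progression lowers it.
- *Phase V's between-arm result is biased.* Phase V has no control arm, and its initial diagnosis is recorded before the model is seen.

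A reader might also argue that urban and rural differences in resources shift the label. Section 2.1.2 does not mention ICU capacity, and randomisation is stratified by that tier, so this would bear on the subgroup comparisons and not on the primary contrast.

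**Conclusion.** The point holds conditionally. ICU admission alone suffices for the severe label. If Phase IV clinicians assess live patients, as the text mostly indicates, the AI-informed call can influence that label in the assisted arm, and adjudicator blinding does not prevent it. The primary AUC difference may then be biased upward or downward. Under the assumed prevalences and reaction rates the shift is a few hundredths: immaterial to a trial with no true effect, but enough to decide the result when the true difference is near 0.15, which is where the trial is planned. Neither the size nor the net direction can be derived from the document. In Phase V the same issue is confined to model concordance and the pre- versus post-model comparison.

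**What to change.** Keep the stated endpoint and make these changes in sections 2.4.5 and 2.8.5:

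1. Have the panel record which component each case met (ICU admission, mechanical ventilation or death).
2. Pre-specify the Phase IV primary comparison repeated with mechanical ventilation or death only as the severe label. These events depend less on the clinician's call than ICU admission does, although averted progression can still affect them.
3. Report ICU admission rates by arm beside the AUC difference.
4. State in advance that the conclusion on diagnostic accuracy will be limited if the two analyses disagree.

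The cost is a few sentences, one panel field and one additional analysis, using events that the panel already verifies. The downside is fewer endpoint cases and a wider interval in the repeated analysis, so it serves as a check and does not replace the primary analysis.

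Re-adjudicating severity from physiological findings is not recommended here. It could build model inputs into the reference standard, would depart from the label used to train the model, and may need data that Table 2 does not list.

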### Sample size

2.5

#### Calculation rationale

2.5.1

The sample size was determined based on the primary outcome (AUC comparison between model-assisted and clinician-only diagnoses) using a two-group superiority design. Key parameters were derived from prior studies on AI diagnostic tools (31, 32):

Expected effect size: ΔAUC = 0.15 (clinically meaningful improvement).

Type I error (*α*): 0.05 (two-tailed).

Power (1-*β*): 0.95.

Attrition rate: 20% adjustment for patient dropout or incomplete data.

The minimum sample size for AUC comparison was calculated using the following formula (33):

$$n=\frac{{\left(Z_{1-\alpha /2}+Z_{1-\beta }\right)}^{2}\times [\mathrm{AU}C_{1}(1-\mathrm{AU}C_{1})+\mathrm{AU}C_{2}(1-\mathrm{AU}C_{2})]}{{\left(\mathrm{AU}C_{1}-\mathrm{AU}C_{2}\right)}^{2}}$$

Where:

$\mathrm{AU}C_{1}$
 (model-assisted): 0.85 (34).

$\mathrm{AU}C_{2}$
 (clinician-only): 0.70 (null hypothesis).

$Z_{1-\alpha /2}$
= 1.96, 
$Z_{1-\beta }$
= 1.645.

#### Sample size derivation

2.5.2

The sample size calculation began with an initial estimate of 145 patients per group (290 total), derived from a power analysis targeting a clinically significant ΔAUC of 0.15 (*α* = 0.05, *β* = 0.95). To account for potential 20% attrition due to incomplete data or participant dropout, the final patient sample was adjusted to 174 per group (348 total). For clinicians, a minimum of 218 participants (109 per group) was required to ensure balanced representation across experience levels (resident, attending, chief) while addressing hospital-level clustering effects, as recommended by methodology for cluster-randomized trials (35). This dual-tiered approach balances statistical precision with pragmatic considerations, ensuring robust evaluation of the AI model’s impact in diverse clinical environments.

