#### Justification

2.5.4

The patient sample size was determined through a power analysis to ensure ≥80% statistical power for detecting a clinically meaningful improvement (ΔAUC more than 0.15) in diagnostic accuracy, aligning with FDA guidelines for validating AI-driven medical devices (36).

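### The printed formula and inputs give 195 patients per group, not 145; with attrition also under-inflated, the planned 348 patients give about 86% power rather than the stated 95%

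*Protocol article*

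**What the plan says.** All of this is in section 2.5 of the protocol article.

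- **2.5.1 (Calculation rationale)** sets out a two-group superiority design and prints a formula with every input: AUC 0.85 for model-assisted diagnosis, AUC 0.70 for clinicians alone, Z values of 1.96 and 1.645, "Type I error (*α*): 0.05 (two-tailed"), and "Power (1-*β*): 0.95". It adds: "Attrition rate: 20% adjustment for patient dropout or incomplete data".
- **2.5.2 (Sample size derivation)** gives the result: "The sample size calculation began with an initial estimate of 145 patients per group (290 total"). It labels the 0.95 as β here, although section 2.5.1 gives the same value as 1 − β. After the attrition step, "the final patient sample was adjusted to 174 per group (348 total").
- **2.5.3 (Final allocation)** fixes enrolment at 348 patients.
- **2.5.4 (Justification)** describes the target differently: "The patient sample size was determined through a power analysis to ensure ≥80% statistical power".

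**The concern.** The formula, its inputs and its result are all printed, so they should agree. They do not, and the attrition step and the power statements add further inconsistencies.

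This calculation is the only stated basis for the patient sample size of the primary AUC comparison. If the power is not what section 2.5.1 says, a result that fails to show a difference would be read as coming from a trial with a 5% type II error when the actual figure is larger.

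**Working it through.** **Inputs (section 2.5.1).** AUC1 = 0.85, AUC2 = 0.70, difference 0.15, two-sided alpha 0.05 (Z = 1.96), power 0.95 (Z = 1.645), attrition 20%.

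**1. The plan's own formula**

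n = (Z₁₋α/₂ + Z₁₋β)² × [AUC1(1 − AUC1) + AUC2(1 − AUC2)] / (AUC1 − AUC2)²

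- (1.96 + 1.645)² = 3.605² = 12.996
- 0.85 × 0.15 + 0.70 × 0.30 = 0.1275 + 0.2100 = 0.3375
- 0.15² = 0.0225
- n = 12.996 × 0.3375 / 0.0225 = 12.996 × 15 = 194.94, so **195 per group (390 total)**

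The stated 145 is not reproduced. It is 50 short, or 50/195 = 26%.

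**2. Can another standard variant give 145?**

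| Variant | n per group |
|---|---|
| Two-sided 0.05, 95% power, pooled variance | 199 |
| The same with continuity correction | 212 |
| One-sided 0.05, 95% power: unpooled / pooled / continuity-corrected | 163 / 166 / 179 |
| Printed formula, two-sided, power 80% / 85% / 90% | 118 / 135 / 158 |

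Figures close to 145 appear only when the printed formula or inputs are abandoned:

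- 148, using AUC1's variance for both arms at 95% power;
- 147, using AUC2's variance for both arms at 80% power;
- 144, with a one-sided test, 90% power and a continuity correction.

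The document describes none of these.

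**3. Attrition**

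- As done: 145 × 1.20 = 174. After a 20% loss, 174 × 0.80 = 139.2 remain, below the plan's own 145.
- To keep 145 evaluable: 145 / 0.80 = 181.25, so 182.
- To keep 195 evaluable: 195 / 0.80 = 243.75, so 244 per group (488 total).

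**4. Power implied by the printed formula**

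Inverting the formula gives power = Φ(0.15 / √(0.3375/n) − 1.96) = Φ(√(n/15) − 1.96).

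| n per group | Meaning | Power |
|---|---|---|
| 139 | 174 enrolled, 20% lost | 86.1% |
| 145 | stated evaluable number | 87.5% |
| 174 | no loss at all | 92.6% |
| 195 | formula result | 95.0% |

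**5. The variance term**

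AUC(1 − AUC)/n treats each patient as one Bernoulli trial. The precision of an AUC depends on the numbers of severe (n₁) and non-severe (n₀) cases, and the formula contains neither. The Hanley–McNeil variance is

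Var(A) = [A(1 − A) + (n₁ − 1)(Q₁ − A²) + (n₀ − 1)(Q₂ − A²)] / (n₁n₀), with Q₁ = A/(2 − A) and Q₂ = 2A²/(1 + A).

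With independent arms of 139, power is Φ(0.15/SE − 1.96). The document gives no severe fraction, so a range is assumed:

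| Assumed severe fraction | SE of the AUC difference | Power |
|---|---|---|
| 10% | 0.105 | about 30% |
| 20% | 0.076 | about 50% |
| 30% | 0.065 | about 64% |
| 50% | 0.055 | about 77% |

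**The case against.** The strongest reply is that section 2.5.4 promises only 80% power, and by the printed formula 139 or 145 evaluable patients exceed that. This is true, and the shortfall is against the 0.95 in section 2.5.1. It does not explain the number, however: at 80% power the formula gives 118. Neither stated target produces 145, and the two targets conflict.

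Several narrower points are fair:

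- The value of 0.95 given for β in section 2.5.2 is evidently a mislabelled 1 − β, not a third power target.
- The attrition error is small. It amounts to 8 patients per group (182 against 174) and about 1.4 percentage points of power (87.5% to 86.1%). The gap between 145 and 195 is the main defect.
- The case-count figures rest on an assumed severe fraction and one AUC per independent arm. The planned analysis is multi-reader, multi-case, with 218 clinicians, and Phase IV randomises clinicians. Readings per case and reader and case correlations do not enter the calculation. The figures show that the formula is inadequate; they do not estimate this trial's power.
- Section 2.5.3 says the 348 patients come from both retrospective and prospective cohorts, so the text does not establish that Phase IV has 174 per arm. That does not help the plan: if fewer belong to Phase IV, power there by the same formula is lower.

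**Conclusion.** The concern holds. With its own formula and inputs the plan needs 195 evaluable patients per group, against a stated 145. With the planned 174 per group and 20% loss, power is 86.1%, a type II error of about 14% instead of 5%. The stated 95% is not reached even with no attrition (92.6%). Reaching it after 20% loss would take 244 per group, or 488 − 348 = 140 more patients than planned.

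These results rest only on figures printed in the protocol. The further loss of power under a case-count variance depends on the severe fraction. It is illustrative, but it points the same way: at every fraction tried, power falls below even the 80% in section 2.5.4.

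**What to change.** Correct sections 2.5.1 to 2.5.4 so that formula, inputs, result and power agree.

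1. Choose one power figure, use it throughout, and delete the statement that β is 0.95.
2. Apply attrition as n/(1 − 0.20).
3. Either keep 348 patients and restate the power (86% by the printed formula after 20% loss), or state 195 evaluable and 244 enrolled per group.
4. Replace the AUC(1 − AUC) variance with one based on the expected severe and non-severe counts, state the assumed severe fraction, and report the resulting power. Once this is done, its results supersede both the 86% and the 244 in step 3, which hold only under the printed formula.

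Keeping 348 and restating the power costs a rewrite of section 2.5 and a less favourable power statement, with no extra patients. Keeping 95% costs 140 more patients by the printed formula, and possibly more once the variance is replaced.

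### The formula and inputs in section 2.5.1 give 195 evaluable patients per group, not the 145 stated in section 2.5.2, so the planned size does not deliver the stated 95% power

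*Protocol article*

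**What the plan says.** Section 2.5.1 (Calculation rationale) sets the design values: "Expected effect size: ΔAUC = 0.15 (clinically meaningful improvement"), "Type I error (*α*): 0.05 (two-tailed") and "Power (1-*β*): 0.95". It assumes an AUC of 0.85 for model-assisted diagnosis and 0.70 for clinicians alone, prints a formula for n, and gives the two Z values as 1.96 and 1.645.

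Section 2.5.2 (Sample size derivation) gives the result: "The sample size calculation began with an initial estimate of 145 patients per group (290 total"). It describes the power analysis as "targeting a clinically significant ΔAUC of 0.15 (*α* = 0.05, *β* = 0.95"). It then raises 145 to 174 per group, 348 in all, for 20% attrition. Section 2.5.3 fixes enrolment at 348.

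Section 2.5.4 (Justification) says the patient number was chosen "to ensure ≥80% statistical power for detecting a clinically meaningful improvement (ΔAUC more than 0.15").

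**The concern.** The formula, every input and the result stand in adjacent sections, so the result can be checked by hand, and it does not reproduce. The figure is the starting point for the whole patient number: 174 is 145 × 1.2, and 348 is 2 × 174.

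What is at stake is the power claim. A reader of section 2.5.1 takes it that a true AUC difference of 0.15 would be missed 5% of the time. By the protocol's own formula the risk at the planned size is higher. The wording around power does not help the reader to see this. Section 2.5.2 gives 0.95 as the value of β, which taken literally means 5% power, and section 2.5.4 uses a looser figure than section 2.5.1.

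**Working it through.** **Inputs, all from section 2.5.1.** AUC1 = 0.85; AUC2 = 0.70; difference = 0.15; Z for two-sided α of 0.05 = 1.96; Z for power 0.95 = 1.645.

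**The protocol's formula.** n per group = (Z₁₋α/₂ + Z₁₋β)² × [AUC1(1 − AUC1) + AUC2(1 − AUC2)] / (AUC1 − AUC2)²

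- (1.96 + 1.645)² = 3.605² = 12.996
- 0.85 × 0.15 + 0.70 × 0.30 = 0.1275 + 0.2100 = 0.3375
- 0.15² = 0.0225
- n = 12.996 × 0.3375 / 0.0225 = 194.94, so 195 per group

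The stated 145 is 50 lower, or 50/195 = 26%. Rounding cannot explain that.

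**Does another standard reading give 145?** With two-sided α of 0.05, the number per group is:

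| Power | Protocol's formula | Pooled variance | Continuity-corrected |
|---|---|---|---|
| 80% | 118 | 121 | 134 |
| 85% | 135 | 138 | 151 |
| 90% | 158 | 161 | 174 |
| 95% | 195 | 199 | 212 |

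One-sided α of 0.05 at 95% power gives 163, 166 and 179 in the same order. Taking β literally as 0.95 gives about 2 per group. None of these is 145.

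**Power at the planned size, by the same formula.** Since 0.3375/0.0225 = 15, power = Φ(√(n/15) − 1.96).

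| Evaluable per group | How it arises | √(n/15) − 1.96 | Power | Risk of missing a true 0.15 |
|---|---|---|---|---|
| 139 | 174 × 0.8 = 139.2 | 1.084 | 86.1% | 13.9% |
| 145 | stated initial estimate | 1.149 | 87.5% | 12.5% |
| 174 | no loss at all | 1.446 | 92.6% | 7.4% |
| 195 | formula at 95% power | 1.646 | 95.0% | 5.0% |

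**Attrition.** Multiplying by 1.2 does not preserve 145 under a 20% loss: 174 × 0.8 leaves 139. Keeping 145 would take 145/0.8 = 181.25, so 182 per group. With 174 enrolled, 145 remain only if 29/174 = 17% are lost.

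**Enrolment that goes with 95% power.** 195 × 1.2 = 234 per group (468 in total) by the protocol's own inflation, or 195/0.8 = 243.75, so 244 per group (488 in total). The plan has 174 per group (348 in total).

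**The case against.** The strongest reply is that the design meets a power statement the protocol itself makes. Section 2.5.4 asks only for at least 80%, and by the stated formula the planned size gives 86% to 93%. That stands, and it limits the consequence: the shortfall is against the 95% claim alone. It does not rescue 145, because the formula at 80% power gives 118.

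A reader might infer that power is stated in three incompatible ways. The text does not support that. A design with 95% power also satisfies a floor of 80%, so sections 2.5.1 and 2.5.4 differ in target without strictly contradicting each other. Only the β in section 2.5.2 contradicts the rest. It is evidently a slip for 1 − β, since section 2.5.1 labels the same 0.95 as power and pairs it with Z = 1.645.

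A reader might also quote 87.5% as the power of the planned trial. That figure belongs to 145 evaluable per group. With 174 enrolled, it holds neither under full retention (92.6%) nor under the protocol's own 20% loss (86.1%).

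It is tempting to explain the error too. Putting 0.25 in place of 0.3375 gives 12.996 × 0.25 / 0.0225 = 144.4, which rounds up to 145. The protocol never mentions 0.25, and other undocumented changes of input land nearby (143, 144, 147, 148). The origin of 145 is unknown.

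Lastly, the formula treats each AUC as a binomial proportion, while the analysis is a multi-reader one and section 2.5.2 mentions hospital-level clustering. Any figure restated from it is therefore power by that formula only. That caveat stands, but whether the formula suits the design is a separate matter and does not affect the arithmetic.

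**Conclusion.** The sample size is wrong as written. The stated formula and inputs give 195 evaluable patients per group, and the protocol reports 145. Hence 145, 174 and 348 do not follow from the calculation shown, and the planned size does not reach 95% power under any retention.

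By the protocol's own formula, power is 86.1% after the planned 20% loss and 92.6% with no loss. The risk of missing a true difference of 0.15 is then 13.9% or 7.4%, against the stated 5%: about 2.8 or 1.5 times as large. It would go too far to call the trial underpowered on this ground, since each of these figures is above the 80% floor.

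The conclusion rests on the assumed AUCs of 0.85 and 0.70, two-sided α of 0.05 and the formula as printed. It makes no claim about the power of the planned multi-reader analysis.

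**What to change.** Keep 348 and state one power figure in sections 2.5.1, 2.5.2 and 2.5.4, tied to the number evaluable: about 86% with 139 evaluable per group after 20% loss from 174, by the stated formula. The 87.5% at 145 evaluable may be given beside it. Specifically:

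- Section 2.5.1: replace the power of 0.95, and the Z of 1.645 that goes with it (about 1.08 at 86%).
- Section 2.5.2: change the value of β to the matching one (about 0.14), and stop presenting 145 as the formula's result at 95% power.
- Section 2.5.4: replace the 80% floor with the same figure.

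This costs wording only; the price is a less favourable stated power.

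If the 95% claim is to stay, the number to state is 195 evaluable per group. Enrolment then becomes 234 per group with the protocol's × 1.2, or 244 with division by 0.8, and the 348 in sections 2.5.2 and 2.5.3 changes to 468 or 488. That means 120 or 140 more patients. The β in section 2.5.2 needs correcting in either case.
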